### Formative Research and Pilot Studies

Before designing the Baduta program, GAIN conducted formative research to identify delivery platforms, create communication strategies and frame messages, and develop communication materials [33]. The GAIN staff and a research team from the London School of Hygiene and Tropical Medicine, London, United Kingdom, and the Regional Centre for Food and Nutrition, Southeast Asian Ministers of Education Organization (SEAMEO-RECFON), Jakarta, Indonesia, conducted formative research and a pilot study of the Healthy Gossip Movement (Gerakan Rumpi Sehat) intervention [33] to determine whether a communication strategy that focused on strong behavioral handles rather than educational messages would be effective in changing nutritional behavior. The Baduta project team developed 12 participative and demonstrative activities for delivery in community settings called *Emo-Demos*. The *Evo-Eco* theory [34] underpins these activities, which are grounded in the psychological and environmental determinants of behavior. This approach suited a community setting where nutrition knowledge was high, but the adoption of healthy nutritional behaviors was poor [35]. The pilot study found a greater improvement in dietary diversity when messaging based on emotional drivers of behavior change was channeled through both mass media TV adverts and *Emo-Demo* community activities [33]. We used these 2 interventions in the package of behavior change interventions for the Baduta program.

### Description of the Baduta Program Interventions

The interventions will primarily aim to strengthen the existing activities delivered through the public health system to promote recommended nutrition practices for pregnancy, breastfeeding, and complementary feeding. We will implement the following activities in the intervention subdistrict clusters during the study.

#### Health System Strengthening Interventions

In the first health system strengthening intervention, Save the Children will launch the implementation of the Baby-Friendly Hospital Initiative (BFHI) [36] in the public sector district and municipal hospitals and birthing centers at the community health centers in the intervention subdistricts. The World Health Organization (WHO) and the United Nations Children’s Emergency Fund (UNICEF) jointly conceived the BFHI in 1991 as a strategy to improve breastfeeding rates worldwide. A hospital or birth center can receive Baby-Friendly designation if they show compliance with the Ten Steps to Successful Breastfeeding [36].

In the second health system strengthening intervention, Save the Children will train village midwives, health workers, and integrated village health post cadres on counseling for appropriate IYCF using the Indonesian Ministry of Health adaptation of the WHO/UNICEF Community Infant and Young Child Feeding Counseling Package [37].

#### Behavior Change Interventions

We will employ 4 different behavior change interventions to address program outcomes, as shown in the program impact pathway (Figure 1). We have developed behavior change communications using the Behavior Centered Design theory and employed emotional drivers of behavior change rather than education-focused messaging [33].

The first will be 12 participative and demonstrative behavior change activities called *Emo-Demos*, developed by the London School of Hygiene and Tropical Medicine, London, United Kingdom, and GAIN [33], which are based on the psychological and environmental determinants of behavior. The Emo-Demos include topics on nutrition during pregnancy (3 activities), breastfeeding (3 activities), care during pregnancy (1 activity), complementary feeding issues (4 activities), and handwashing (1 activity; see Multimedia Appendices 2 and 3 for details of Emo-Demos). The Paramitra Foundation will recruit and train village facilitators to train village midwives and health cadres to deliver Emo-Demos during monthly pregnant women classes and child growth monitoring at the integrated village health post.

The second will be a national TV campaign that will have 4 high-quality spots with messages on nutrition during pregnancy (1 spot), breastfeeding (1 spot), and complementary feeding issues (2 spots; see Multimedia Appendices 4 and 5 for a description of these TV spot messages). The TV spots will air on 5 national TV channels, and it will not be possible to contain them to only the intervention subdistricts. Village facilitators will also screen the TV spots using tablets during integrated village health post meetings and with people passing by during *street visits*.

The third will be the established SMS Bunda intervention, a free, text message service for pregnant women and postnatal mothers that aims to reduce maternal and infant mortality [38]. Midwives encourage women to access the service by registering their mobile number and the expected date of delivery at any time during pregnancy. Initially, in pregnancy, the women receive regular short messages about antenatal care. In the last month of pregnancy, the text message contains information related to the first days after childbirth for mother and baby, including information about early initiation of breastfeeding. In the first month of birth, the messages provide information about the health of mothers and newborns, including exclusive breastfeeding.

In the fourth intervention, GAIN will partner with a company, Nazava, to expand sales of low-cost water filters and promote appropriate water treatment and hygiene practices. Water filters are a low-cost and effective method to purify water that avoids costly fuels (wood or electricity) to boil water. Nazava’s rural sales network in the Malang and Sidoarjo districts as well as trained resellers will market the filters and provide education sessions on water treatment and handwashing.

### Description of Standard Primary Health Care Services

During the study, both the intervention and the comparison clusters will receive the standard primary health care services. Monthly integrated village health posts are the delivery platforms for the usual community health services that include child growth monitoring, food supplements, child immunizations, antenatal care, pregnancy classes, and family planning services. The local community, particularly the village health cadres, organize the integrated village health post services under the supervision of the community health center staff. The community health center staff, village midwives, and village health cadres deliver the services.

### Evaluation Outcomes

#### Primary Outcomes

The primary outcome for the cross-sectional evaluation is the difference in the percentage of stunted (length-for-age<–2 Z scores) children aged 0-23 months between the intervention and the comparison groups at the baseline and end-line surveys. For the cohort evaluation, the primary outcome is the difference in the mean length-for-age Z scores between the intervention and the comparison groups every 3 months from birth to 18 months, as measured in the follow-up assessments.

#### Secondary Outcomes

The secondary outcomes for the cross-sectional evaluation include differences between the 2 treatment groups at the baseline and end-line surveys in the following: (1) the percentage of wasted (weight-for-length<–2 Z scores) children aged 0-23 months and their mean weight-for-length Z scores; (2) the percentage of children aged 0-23 months with low hemoglobin (Hb <11 g/dL) and their mean hemoglobin; (3) the number of events and the mean number of days the children are ill >2 weeks before interview with diarrhea, acute respiratory infections, and fever; (4) the percentage of children aged 0-23 months who are ever breastfed, are breastfed with an hour of birth, are given prelacteal feeds, are exclusively breastfed in the first 6 months of life, continue breastfeeding at 1 and 2 years, and are age appropriately breastfed; (5) the percentage of children aged 6-23 months with minimum dietary diversity, minimum meal frequency, minimum acceptable diet, and frequency of consumption of 7 food groups and iron-rich foods; (6) the percentage of children aged 6-23 months consuming snacks the day before the interview; (7) the mean intake of food energy, protein, carbohydrate, fat, and selected micronutrients from complementary foods and the micronutrient density of the complementary feeding diets compared with desired levels at 6-8, 9-11, and 12-23 months of age; (8) the percentage of children aged 12-23 months at risk of inadequate nutrient intake; (9) the percentage of mothers with appropriate knowledge about IYCF; and (10) the percentage of mothers with high self-efficacy for breastfeeding.

The secondary outcomes for the cohort evaluation include differences between the 2 treatment groups in the following: (1) the percentage of wasted (weight-for-length<–2 Z scores) children and their mean weight-for-length Z scores every 3 months from 3 to 18 months; (2) the percentage of children with low hemoglobin (Hb <11 g/dL) and their mean hemoglobin at 18 months of age; (3) the number of events and the mean number of days the children are ill >2 weeks before interview with diarrhea, acute respiratory infections, and fever from birth to 18 months; (4) the percentage of children who are ever breastfed, are breastfed within 1 hour of birth, are given prelacteal feeds, and are exclusively breastfed each month from birth to 6 months; (5) the median maternal breastfeeding self-efficacy score and the percentage of mothers with high self-efficacy for breastfeeding at 7 days and 3 and 6 months postpartum; (6) the percentage of children with minimum dietary diversity, minimum meal frequency, and minimum acceptable diet at 7, 10, and 17 months of age; (7) the percentage of children consuming snacks within 1 hour of meals and the contribution of snacks to energy intake at 6-8, 9-11, and 16-18 months of age; (8) the mean intake of food energy, protein, carbohydrate, fat, and selected micronutrients from complementary foods and the micronutrient density of the complementary feeding diets compared with desired levels at 6-8, 9-11, and 12-23 months of age; (9) the percentage of women receiving and consuming iron and folic acid supplements during pregnancy; and (10) the percentage of women pregnant in their third trimester meeting minimum dietary diversity and at risk of inadequate nutrient intakes.

### Outcome Measurements

In the cross-sectional assessment at baseline and end-line surveys, we will measure the following factors or indicators: social, economic, and demographic characteristics; infant feeding practices; child morbidity; contact with the health system; and exposure to the interventions. We will also measure maternal and child anthropometry and hemoglobin status.

In the cohort assessment, we will conduct repeated data collection on social, economic, and demographic characteristics; infant feeding practices; maternal and child dietary intake; child morbidity; contact with the health system; and exposure to the interventions. We will also conduct repeated measurements of maternal and child anthropometry and child hemoglobin status at 18 months.

#### Anthropometry

Trained field workers will collect measurements of weight, recumbent length in infants, height in mothers, and mid-upper arm circumference in pregnant women using standard methods and equipment [39,40]. We will standardize the measurements of the anthropometry field workers using established methods before and during data collection [39]. In both the cross-sectional and cohort evaluations, 2 field workers will collect duplicate measurements of the weight and length of children aged <2 years. The field workers will take a third measurement if the difference between the first 2 measurements exceeds a predetermined allowable limit (see details below).

We will calculate the Z scores for infant length-for-age and weight-for-length using the 2006 WHO Child Growth Standard [41], and we will define stunting as a low length-for-age or <−2.00 SD from the reference mean and wasting as low weight-for-length or <−2.00 SD. We will collect mid-upper arm circumference from pregnant mothers and define it as low if <23 cm [42].

The field workers will collect all anthropometry data using in-field digital data capture on tablets with routines that immediately calculate Z scores and provide them with a warning about extreme values and the need for remeasurement to check for potential errors (ie, if first and second measurement differed by >0.7 cm for length and by >0.1 kg for weight). We will refer to children with very low weight-for-height (Z score<−3) to their local community health center for assessment and treatment of severe acute malnutrition.

#### Birth Weight and Duration of Gestation

In the cross-sectional assessment, we will ask mothers of children aged <2 years to recall the birth weight and ask them to describe their infant’s birth size using the same question as in the Indonesian Demographic and Health Survey (DHS) [43]. There will be no estimate of the duration of gestation. In the cohort assessment, we will measure birth weight within 72 hours after birth. We will estimate the duration of gestation using the mother’s report of the first date of her last menstrual period.

#### Hemoglobin

In the cross-sectional evaluation, we will assess hemoglobin in all women and children. However, in the cohort evaluation we will assess hemoglobin from children at 18 months and mothers during pregnancy. We will collect capillary blood samples and measure hemoglobin using a portable hemoglobinometer (Hemocue). We will refer mothers with a hemoglobin level <12 g/dL and children with a hemoglobin level <11 g/dL to their local community health center for assessment and treatment.

#### Child Morbidity

In the cross-sectional and cohort assessments at the scheduled visits (Figure 3), trained interviewers will record maternal recall of symptoms from the preceding 2 weeks of common childhood illnesses (diarrhea, cough, and fever) using the standard Indonesian DHS questions.

**Figure 3 figure3:**
[figure not shown]
Schedule of enrollment, interventions, and assessments for cohort evaluation. X: indicates activity occurred at given visit or life cycle stage; lines mark the duration of the interventions; 24 HR: 24-hour dietary recall.

#### IYCF

In both the cross-sectional and cohort evaluations, we will collect information about IYCF using an interviewer-administered questionnaire on breastfeeding and general complementary feeding practices. In the cross-sectional evaluation, trained interviewers will ask questions about infant feeding practices based on questions from the Indonesian DHS that allow estimation of the standard WHO IYCF indicators [44]. These IYCF questions will include the timing of initiation of breastfeeding; current breastfeeding status; use of bottles for feeding; current use, timing, and introduction of other liquids and solid foods; meal frequency; and consumption of food groups in the previous 24 hours and week before the interview. We will also collect 24-hour dietary recalls (24-HR), which will be used to assess indicators of IYCF (see the Dietary Intake Data section).

In the cohort assessment, we will administer the questions about IYCF at the same time as we collect the anthropometric data, that is, soon after birth, every month in the first 6 months, then every 3 months until they are 18 months of age.

We will estimate indicators of IYCF according to the WHO indicators for assessing IYCF practices [44], including early initiation of breastfeeding, exclusive breastfeeding, predominant and continued breastfeeding, bottle-feeding practices, dietary diversity score, meal frequency, minimal acceptable diet, and timing of initiation of complementary feeding.

Information will be collected about mothers’ intentions to breastfeed their infants when they are pregnant. We will assess the mothers’ self-efficacy with breastfeeding using the breastfeeding self-efficacy short questionnaire developed by Dennis [45], which is a 14-item instrument aimed at measuring breastfeeding confidence, at birth and at 1, 3, and 6 months postpartum.

#### Dietary Intake Data

Quantitative dietary intake data will be collected using 4-pass 24-HR. In the cross-sectional evaluation, we will collect it at baseline and end line from pregnant women and infants aged 6-23 months, whereas in the cohort assessment, we will collect it from mothers during pregnancy (third trimester) and from infants at 7, 10, and 17 months of age. Paper-based data collection was used to collect dietary data in the cross-sectional surveys and for the pregnant women in the cohort study, whereas digital data capture was used to collect the 24-HR from children in the cohort study.

For each target group and data collection period, 24-HRs will be proportionately collected on all days of the week to account for any day of the week effects on dietary intakes. In subsamples of pregnant women and infants aged 12-23 months, we will collect repeated 24-HRs on nonconsecutive days (n=40 per target group per data collection period) to adjust nutrient intake distributions for intrasubject variability [46] when estimating the percentage at risk of inadequate nutrient intakes.

We will collect all 24-HRs in the participants’ homes by trained interviewers using standardized methods [46]. Briefly, in the *first pass*, each respondent will be asked to recall all foods and beverages consumed by herself (or her child) during the preceding day. In the *second pass*, for each food and beverage listed, we will record details about the time of consumption, the food and beverage (brand names, ingredients, and cooking methods), and any food items added (eg, sugar added to tea). In the *third pass*, we will ask the respondents to estimate the amount they (or their child) consumed, after probing for leftovers. Portion sizes will be quantified by weighing the indicated amounts of real foods, photographs, food models, or by the number of standard units consumed. We will develop a standard portion size manual to ensure that all interviewers use consistent methods. We will record recipes, including the amounts of raw food used in the recipe, the cooking method, and the total amounts cooked and consumed. In the *fourth pass*, the interviewers will review the dietary data for completeness, and they will ask whether the previous day’s diet represented a typical day and, if not, how it differed from usual, and for infants, whether they were breastfed on the previous day.

#### Dietary Data Processing

Dietary data will be collected using either a paper-based questionnaire or an in-field digital data capture on tablets for multiple-pass 24-HR that is under development. The digital data capture system saves data processing time and reduces errors by ensuring that probes and food portion size estimations are standardized. At the end of each data collection day, all dietary data will be checked for completeness by the team supervisor. Paper-based questionnaires will be entered into computer files with special-purpose data entry screens, and digitally captured questionnaires will be downloaded directly to a central server. The 24-HR records from both sources will be reviewed by trained nutritionists to monitor data quality and to select the appropriate food composition for foods not linked to an existing food composition item. We will monitor dietary data quality by applying a plausible energy range for children (by age group and breastfeeding status) to identify energy under- and over-reporting.

### Process Evaluation

Process evaluation of the Baduta study aims to assess program coverage, fidelity, and acceptance by the intended target population, guided by the program impact pathway, and to demonstrate plausibility and the attribution of impacts to the intervention. We will emphasize the 4 program impact pathways that include knowledge adoption of (1) exclusive breastfeeding, (2) IYCF practices, (3) iron intake pathway, and (4) knowledge adoption of household water treatment and safe storage and hand washing. In the process evaluation, we will collect data about the interventions attached to these 4 pathways, such as the BFHI, breastfeeding and complementary feeding counseling, emotional demonstration (Emo-Demo), and enhanced water treatment through the household-level promotion of Nazava water filters.

We will use mixed methods to collect process evaluation data. The qualitative methods will include semistructured interviews with women participating in the intervention, health workers (midwives, nurses, village midwives, cadres, nutritionists, and doctors), managers (the head of the community health center and the head of midwives), and intervention implementers (Project Manager, Monitoring Officer, and Field Officer of Save the Children; Director, Project Manager, Monitoring Officer, and Subdistrict Coordinator of Paramitra; and Project Manager, Safe Eater Consultant, and Save Water Entrepreneur of Nazava); a structured questionnaire survey of the water filter users; and observation of Emo-Demo sessions. Apart from these primary data, we will use secondary data from the project monitoring records maintained by Save the Children, Paramitra, and Nazava.

The field research team will consist of nutritionists, anthropologists, and psychologists who have previous experience in qualitative research and speak the local language. The investigators from the University of Indonesia, SEAMEO-RECFON, and the University of Sydney will train the field research team in qualitative data collection, data organization methods, and survey methods. They will be involved in finalizing the data collection tools that will be pretested before data collection. We will purposively select a sample of the clusters from the evaluation study to collect the process evaluation data.

### Sampling Design and Sample Size

#### Sample Size

We estimated the targeted sample size for the study using the following assumptions: (1) in the 51 subdistricts in the Malang and Sidoarjo districts, there is a total population of approximately 4.4 million, with an average of approximately 86,000 per subdistrict; (2) assuming a crude birth rate of 17 per 1000 population per annum, 5% refuse, and 10% data losses, each subdistrict cluster would yield an average of 620 live births over 6 months; (3) an expected prevalence of stunting for children aged 0-23 months of 35% in the control clusters (based on unpublished survey data from Brebes, West Java, and Indonesian DHS data); (4) 80% power and 5% 2-sided alpha, and 1:1 ratio of interventions (subdistricts with and without the Baduta program) allocated; (5) design effect of 1.5 (lower than reported for the 2011 Indonesia DHS survey because of larger sized clusters); and (6) expected percentage point difference in the prevalence of stunting (0-23 months) between the intervention groups of 6% (35.0% in the control to 28.9% in the intervention group). (This is a relative reduction of 17%, which is lower than the 29% reduction in stunting reported in a recent meta-analysis [47] of education interventions to improve complementary feeding.)

A standard formula using established methods [48] for comparison of proportions to calculate the number of subjects required per intervention arm to test H_0_: *π*_0_=*π*_1_ is as follows:

where *z_α_*_/2_ and *z_β_* are standard normal distribution values for upper tail probabilities of *α*/2 and *β,* respectively, *π*_0_ is the proportion in control, *π*_1_ is the expected proportion in intervention, *m* is the number of individuals per cluster, and *ρ* is the intracluster correlation coefficient.

Based on this calculation, the sample size required is 1392 mother-infant dyads from each group of 6 subdistrict clusters or approximately 232 mother-infant dyads per subdistrict cluster. We will round this up to 2800 mother-infant dyads per cross-sectional survey or 234 per subdistrict cluster. This sample size will provide 80% power assuming a Z score SD of 0.975 and 5% level of significance to detect a 0.15 Z score difference in height-for-age Z scores [49] between the intervention and the control groups in the end-line survey. Therefore, for the cross-sectional evaluation, we will select 2800 mothers of children aged 0-23 months and an additional 400 pregnant women from 12 subdistricts within the Sidoarjo and Malang districts.

For the cohort evaluation, to detect a difference in mean length-for-age Z score between the experimental and control groups at an end line of 0.35 Z score [50], assuming 80% power and 5% level of significance, with a design effect of 1.5 (see above), we will require a sample size of 272 mother-infant pairs in each of the intervention and comparison groups. Assuming a dropout rate of 25%, we need to recruit 680 mother-infant pairs (56-57 per subdistrict cluster).

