### Study Setting

We will perform the study in the Malang and Sidoarjo districts of East Java, Indonesia (see Multimedia Appendix 1—a map of East Java with the study districts marked), which had an estimated population of almost 2 million and 2.5 million in 2014, respectively. There are 350 villages in Sidoarjo and 390 villages in Malang. The population density of Sidoarjo (2891/km^2^) is almost 4 times the population density of Malang (780/km^2^) [27]. Sidoarjo is a peri-urban district, with 13% of households from urban areas, and most adults are employed as factory workers (36%) or providing public and private services (41%: trader, hotels, restaurant, and public institutions) [28]. Malang is a rural district, with 97% of households from rural areas, and most adults are employed as farmers (33%) or providing public and private services (34%: traders, hotels, restaurants, and public institutions) [29]. On the basis of the annual nutrition surveillance data from the Ministry of Health, there are 24% of children aged <5 years who are stunted in Sidoarjo and 31% in Malang. Approximately two-thirds of the children aged <5 years in Malang and a half in Sidoarjo attend integrated village health posts for weight monitoring [28,29].

There are 51 subdistricts available for the study (33 in Malang and 18 in Sidoarjo), with an average population of 86,000. On average, there are 1.3 community health centers in each subdistrict, and each covers a population of approximately 68,000 people. Within the catchment area of each community health center, there are, on average, 2.8 subcenters (*Pustu*) that cover 5 villages or about a population of 30,000. Primary health care outreach to the community uses monthly integrated village health posts organized by local female health volunteers who coordinate with the community health center staff and village midwives. Village midwives are trained midwives who reside in 1 village within the community health center catchment area and are part of the service network. The village midwives’ program is part of the government’s efforts to accelerate the improvement of community health, particularly concerning maternal and child health. The roles and responsibilities of village midwives include maternal and child health, family planning services, health promotion, and preventive services as well as early detection and initial treatment for maternal and child health conditions, including undernutrition.

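### The design effect of 1.5 rests on a reason its own formula does not support, and the sample-size figures imply incompatible clustering, so the 80% power for stunting is unsupported and fragile.

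*Protocol article*

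**What the plan says.** All of the sizing is in the protocol article, under Sampling Design and Sample Size, Sample Size.

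- Stunting comparison: "80% power and 5% 2-sided alpha, and 1:1 ratio of interventions", with "35.0% in the control to 28.9% in the intervention group".
- Clustering: a "design effect of 1.5 (lower than reported for the 2011 Indonesia DHS survey because of larger sized clusters"). The formula's legend defines m as the number of individuals per cluster and says that ρ "is the intracluster correlation coefficient". No value of ρ is given.
- Result: "the sample size required is 1392 mother-infant dyads from each group of 6 subdistrict clusters", or "approximately 232 mother-infant dyads per subdistrict cluster", rounded up to 2800 per survey (1400 per arm).
- The same survey sample is said to give 80% power for a 0.15 difference in height-for-age Z score with SD 0.975. No design effect is named for this statement.
- Cohort, for a 0.35 Z difference: "with a design effect of 1.5 (see above), we will require a sample size of 272 mother-infant pairs" per group, with 680 recruited in total, or 56–57 per subdistrict.

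Cluster Selection and Design of Randomization fixes 12 subdistricts, six per arm. Study Setting reports that "there are 24% of children aged <5 years who are stunted in Sidoarjo and 31% in Malang".

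**The concern.** Three things do not fit together. First, the reason given for a low design effect points the wrong way in the plan's own formula if cluster size means children sampled per cluster. Second, one design effect serves two evaluations whose cluster sizes differ four- to five-fold. Third, the Z-score power statement for the same survey matches a different design effect.

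The stunting comparison carries the primary hypothesis, and its power depends strongly on the design effect. If the true value is well above 1.5, a non-significant result could be taken as evidence against a 6-point reduction when the design had a much weaker chance of detecting one.

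**Working it through.** **1. Reproduce the plan's figure.** Inputs: 0.350 v 0.289, two-sided 5%, 80% power.
- Variance sum: 0.35×0.65 + 0.289×0.711 = 0.4330.
- Unpooled n = 0.4330×(1.960+0.842)²/0.061² ≈ 913 per arm; ×1.5 = 1370.
- Pooled: 917×1.5 = 1375.5. Continuity-corrected: 949×1.5 = 1423.5.

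All are within 3% of 1392. The multiplication is sound; the question is the 1.5.

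**2. ρ implied by 1.5**, from ρ = (DE−1)/(m−1).
- Survey, m = 232: 0.5/231 = 0.0022. At 35% prevalence this is a between-subdistrict SD of √(0.0022×0.35×0.65) ≈ 0.022, or 2.2 percentage points.
- Cohort as analysed, m = 272/6 = 45.3: 0.5/44.3 = 0.0113.
- Cohort as recruited, m = 680/12 = 56.7: 0.5/55.7 = 0.0090.

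Conversely, ρ = 0.0022 would give a cohort design effect of only 1.10–1.12. Applied to the survey (m = 1400/6 = 233.3), the cohort values give 1+232.3×0.0090 = 3.09 and 1+232.3×0.0113 = 3.62.

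**3. Design effect implied by the 0.15 Z statement.**
- Unadjusted n = 2×0.975²×(1.960+0.842)²/0.15² ≈ 663 per arm.
- 1400/663 = 2.11, so 80% power corresponds to a design effect of about 2.1.
- At 1.5 the SE is 0.975×√(2×1.5/1400) = 0.0451, and power is Φ(0.15/0.0451 − 1.96) = 91%.

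**4. Stunting power with 1400 per arm.** SE = √(0.4330×DE/1400). Normal power is Φ(0.061/SE − 1.96). For 12 clusters, the t version uses a non-central t on 10 df (critical value 2.228). The difference detectable with 80% power is 2.802×SE (normal) or 3.110×SE (10 df), with SE held at the planned prevalences.

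| Source of clustering | ρ | DE | SE | Power, normal | Power, 10 df | Detectable, normal | Detectable, 10 df |
|---|---|---|---|---|---|---|---|
| Plan's 1.5 | 0.0022 | 1.50 | 0.0215 | 81% | 72% | 6.0 pts | 6.7 pts |
| 0.15 Z statement | 0.0048 | 2.11 | 0.0255 | 67% | 58% | 7.2 pts | 7.9 pts |
| Cohort, recruited m | 0.0090 | 3.09 | 0.0309 | 51% | 43% | 8.7 pts | 9.6 pts |
| Cohort, analysed m | 0.0113 | 3.62 | 0.0335 | 45% | 38% | 9.4 pts | 10.4 pts |

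In the second row, ρ = (2.11−1)/232.3 = 0.0048.

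**5. District figures as a rough gauge.** If the 24% v 31% gap were the only between-cluster variation and clusters were split evenly, the SD would be 0.5×7 = 3.5 points; with 33/51 of clusters from Malang it would be about 3.3. Both exceed the 2.2 points that the plan's 1.5 allows. The split is an assumption; the article does not give it.

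**The case against.** - **Larger clusters may mean more populous ones.** The section describes subdistricts of about 86,000 people, and bigger units tend to have a lower ρ. This is a fair reading and softens the criticism of the rationale. It does not rescue it: the design effect depends on (m−1)ρ, m is also large, and no ρ is given to show that the product is 0.5.
- **The cohort does not show which ρ is right.** Its outcome is mean length-for-age Z score, not binary stunting, so the correlations need not match. If 0.0022 is right for both, the cohort is conservative and the survey's 80% stands on normal quantiles. The cohort's m is itself unsettled: Study Design speaks of a subset of clusters, and Sampling Procedure of six subdistricts. With six in all, m = 544/6 ≈ 91 and ρ = 0.5/89.7 ≈ 0.0056. All of this stands. What remains is that the cohort calculation offers no basis of its own and simply points back.
- **The 0.15 Z statement may be a loose minimum.** Possibly, but it is worded as what the sample provides, and no design effect is named.
- **The district gap.** A reader might infer that it contradicts the 1.5. The documents do not support that: these are whole-district figures for under-5s, while the trial studies children aged 0–23 months in 12 subdistricts chosen as similar, with allocation constrained on underweight prevalence. They are only a warning sign.
- **The 35% control prevalence.** A reader might infer that 35% is too high and costs power. At a design effect of 1.5 and control prevalence of 24–31%, power is 59–74% if the relative reduction is held, but 90–84% if the 6.1 points are held. The documents do not settle this against the plan.
- **Timing.** Both surveys are complete, and the analysis already promises clustering-adjusted confidence intervals, which show what a null result excludes. Restating power changes no design decision, but it corrects a figure on which interpretation will lean.

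**Conclusion.** The point holds as a fault of justification and consistency, not of multiplication. The stated reason for 1.5 does not follow from the formula, the ρ it needs is not stated, and the survey, cohort and Z-score calculations imply different degrees of clustering with nothing said to reconcile them.

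It would be tempting to conclude that the trial does not have 80% power for stunting. The documents do not establish that on every reading: with a design effect of 1.5 and normal quantiles, the 80% is reproduced. It fails under each other clustering value drawn from the sample-size section, and even at 1.5 once the test allows for 12 clusters. The lowest figures, 51–45% (43–38% on 10 df), rest on carrying the cohort's implied ρ over to stunting, which is an assumption. The 10 df results assume a cluster-level comparison of two groups of six with no further terms.

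**What to change.** 1. Remove the cluster-size rationale, or replace it with an explicit argument about ρ.
2. State a subdistrict-level ICC for stunting and its source. The February 2015 baseline survey (2435 children) can inform it, but 12 clusters estimate an ICC imprecisely, so give its uncertainty.
3. Compute the design effect separately for the survey (m about 233) and for the cohort at its actual m, with an ICC suited to each outcome.
4. Reconcile the 0.15 Z statement: name its design effect, or restate its power.
5. Replace the single 80% with power and detectable difference over ICC values of about 0.002 to 0.011, using 10 df.

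Neither a district term in the primary model nor a range of control prevalences is needed to correct this point.

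Cost: some rewording, an ICC estimate from data already collected and a short table. No participants are added. The stated power becomes less favourable.
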